### Safety evaluation and reporting of adverse events

Analysis of safety related data is performed with respect to frequency of serious adverse events, frequency of serious adverse events stratified by causality and frequency of morbidity in both treatment groups.

From the day the patient has signed informed consent until the regular end of trial at 24 months follow-up or until premature withdrawal of the patient, all serious adverse events will be documented on a "serious adverse event form" available in the investigator site file. A serious adverse event will be defined as an event, that results in death, is immediately life-threatening, requires or prolongs hospitalization or results in persistent or significant disability or incapacity. Serious adverse events will be classified to intensity (mild, moderate, severe), outcome (ongoing, recovered completely, recovered with sequelae, death, unknown) and causality (unrelated; possibly, probably or definitely related to trial intervention; not assessable). The assessment is based on surgical findings and the clinical course of the patient. It needs to be done by the investigators in the participating trial centres. They will be furnished with written recommendations on how to assess causality with trial intervention within the ChroPac trial.

Serious adverse events have to be reported by the attending physician to the principal investigator within 24 hours after the SAE becomes known.

### Statistical methods

#### Sample size calculation

The sample size calculation is based on the primary outcome and the primary analysis for the intention-to-treat population. The prior assumption based on the evaluation of 2 clinical trials is a mean intervention group difference of 10% for the EORTC QLQ-C30 scale "physical functioning" (range 0 to 100) with an estimated standard deviation of 20% 24 months after the surgical intervention [14,15].

With a two-sided level of significance α = 5% and a power of 1-β = 90%, a sample size of 86 patients per intervention group is required to detect this difference with a two-sided Student's t-test. It is assumed that an application of an analysis of covariance in the evaluation will lead to a reduction of the standard deviation. Furthermore, using the average of the EORTC QLQ-C30 scale "physical functioning" measured after 6,12 and 24 months instead of the value 24 months after the surgical intervention will presumably sharpen and stabilize the extent of the intervention group difference as also differences between the intervention groups that occur earlier after the surgery are taken into account. It can therefore be expected that this will increase the actual power of the trial as compared with the power calculated on the basis of the above-mentioned assumptions.

To compensate a potential loss in power caused by withdrawals, the sample size is increased by 15% and hence a total of 200 patients will be randomised.

#### Analysis

The confirmatory analysis is performed for the intention-to-treat (ITT) population.

The two-sided null-hypothesis for the primary outcome measure states that both surgical interventions lead to the same expected average QoL scores during 24 months after surgery. This null-hypothesis will be tested by application of an analysis of covariance that adjusts for age, centre and EORTC QLQ-C30 scale „physical functioning“ before surgery. Missing values will be replaced by multiple imputation [16].

Methods of descriptive data analysis will be used for the secondary outcome measures. Descriptive statistics will be calculated according to the scale level of the variables. Further analyses include the time course of the primary and secondary outcome measures. Additionally, sensitivity analyses will be conducted using different patient populations (per-protocol population excluding patients with relevant protocol violations), different imputation techniques for missing values, and different statistical methods for taking into account covariates. Graphical methods including scatter plots and boxplots will be used to visualize the findings of the trial.

The safety analysis includes calculation of frequencies and rates of complications and serious adverse events reported in the two intervention groups. All analyses will be done using SAS Version 9.1. or higher.

### Withdrawals

Patients are free to withdraw trial participation at their own request at any time and without giving reasons for their decision. Moreover, the primary investigator can withdraw study patients, if continuation of the trial would be detrimental to the patient's well being.

Withdrawals will be documented in the CRF and in the patient's medical records and all ongoing serious adverse events have to be followed up.

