### Randomisation

In order to achieve comparable intervention-groups, patients will be allocated concealed by preoperative randomisation at the day of surgery using a centralised web based tool http://www.randomizer.at. Block randomisation will be performed for each centre to achieve equal group sizes per centre.

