### Blinding

Patients and outcome assessors will be blinded for the trial intervention.

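### Investigator withdrawal ends the recording of new serious adverse events, and nothing requires outcome follow-up to continue, so data related to outcome can be lost

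*Protocol article*

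**What the plan says.** The Withdrawals section gives two routes out of the trial. Patients may leave at their own request, and "the primary investigator can withdraw study patients, if continuation of the trial would be detrimental" to well-being. On what follows, it says: "Withdrawals will be documented in the CRF and in the patient's medical records and all ongoing serious adverse events have to be followed up".

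The section on safety evaluation sets the window for documenting serious adverse events. It opens at informed consent and runs "until the regular end of trial at 24 months follow-up or until premature withdrawal of the patient".

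The sample size section treats withdrawals as a matter of power: "To compensate a potential loss in power caused by withdrawals, the sample size is increased by 15" per cent, giving 200 patients.

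On timing, "patients will be allocated concealed by preoperative randomisation at the day of surgery". Table 1 (study visits) shows that after discharge the scheduled activities are the quality-of-life questionnaire and the assessment of secondary outcomes and safety at 6, 12 and 24 months.

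The confirmatory analysis is by intention to treat with multiple imputation. The Analysis section also announces sensitivity analyses with other imputation techniques, without naming them.

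**The concern.** The intervention is a single operation, so after discharge there is no trial treatment left to stop. Leaving the trial at that stage can only mean leaving follow-up. The criterion for investigator withdrawal is linked to the patient's condition, and the primary outcome is physical functioning. Patients withdrawn on this ground may therefore have worse scores than their earlier data would predict.

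Two things are at stake:

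- **Safety.** New serious adverse events after withdrawal are outside the documentation window, so the planned comparison of event frequencies would rest on incomplete counts. The analysis cannot repair this.
- **Primary outcome.** If scores are lost for reasons that the observed data do not explain, imputation under missing at random fills them with values that are too good. If this happens more often in one group, the group difference is biased. A larger sample does not remove that.

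**Working it through.** **1. The plan's own figures.** Inputs from the sample size section: difference 10 points, SD 20, two-sided 5%, power 90%.

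- Normal approximation: n = 2 × (1.960 + 1.282)² × 20² / 10² = 84.1, so 85 per group.
- Exact t-test: 86 per group (power 0.903). The stated 86 is reproduced.
- Inflation: 86 × 1.15 = 98.9, so 99 per group (198 in total); or 86 / 0.85 = 101.2, so 102 per group (204 in total). The stated 200 lies between the two.
- Loss covered: 200 − 2 × 86 = 28 patients, or 28/200 = 14%.

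The sample size is sound. It covers lost precision only.

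**2. What the article says about each type of data after withdrawal.**

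| Data | After withdrawal |
|---|---|
| New serious adverse events | Documentation ends (Safety evaluation) |
| Ongoing serious adverse events | Followed up (Withdrawals) |
| Quality of life | Not stated; the withdrawal allowance in the sample size section implies some loss |
| Mortality | Counted over the follow-up period (Table 2); whether that period outlasts withdrawal is not stated |
| Other secondary outcomes | Not stated |

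**3. Possible bias in the primary comparison.** The withdrawal rates and score gaps below are assumptions; the article gives neither. Let w₁ and w₂ be the proportions withdrawn in the two groups, and s the number of points by which the withdrawn patients' true average lies below the imputed one. Each group mean is overstated by w × s, so the group difference is biased by

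b = s × (w₂ − w₁).

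Take 100 per group, w₁ = 5%, w₂ = 15% and SD 20, counting only the patients observed and ignoring covariate adjustment:

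- SE = 20 × √(1/95 + 1/85) = 2.99
- Type I error = 1 − Φ(1.96 − b/SE) + Φ(−1.96 − b/SE)
- Power for a true difference of 10, if the bias acts against it = Φ((10 − b)/SE − 1.96)

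| s | b | Type I error | Power |
|---|---|---|---|
| 10 | 10 × 0.10 = 1 | about 6% | about 85% |
| 20 | 20 × 0.10 = 2 | about 10% | about 76% |
| 30 | 30 × 0.10 = 3 | about 17% | about 65% |

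With b = 0 and the same numbers, power is Φ(10/2.99 − 1.96), about 92%. If the excess withdrawals fall in the better group, the bias enlarges the difference instead.

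At 0% v 15% the bias is 1.5 to 4.5 points and the type I error about 8% to 33%. At equal rates and equal deficits (5% v 5%, any s) b = 0.

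**4. A limit on these figures.** They treat s as the gap in the whole three-visit average. A patient withdrawn after the 6-month visit has one observed score. With equal weights, a gap per missing visit then enters the average at two thirds of its size; after the 12-month visit, at one third.

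**The case against.** The strongest reply is that the text supports less than a reader might infer from it.

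- **That all data collection stops.** This is explicit only for new serious adverse events. For quality of life it is implied by the withdrawal allowance. That later deaths go uncounted is an inference too, since mortality has no stated cut-off at withdrawal. The full protocol may say more. This stands, and the point is limited accordingly. The safety cut-off, however, is a rule the article states and not a detail it omits.
- **That the person who withdraws patients knows the allocation.** Under Blinding, "Patients and outcome assessors will be blinded for the trial intervention", so investigators are not listed. On the causality of adverse events, "The assessment is based on surgical findings and the clinical course of the patient. It needs to be done by the investigators" at the centres. Knowledge of the operation is therefore plausible. But the term primary investigator is undefined and may mean a trial-level role, and nothing says whether that person knows the allocation.
- **That the clause is a rule for removing the sickest patients after surgery.** It also covers the time from consent to surgery. Its test is whether continuing the trial harms the patient, not whether the patient is doing badly. When only questionnaires and visits remain, that test may seldom be met. This argues for a low frequency; it does not remove the route.
- **That the whole 14% allowance measures the exposure.** That figure covers all withdrawals in both groups, including those at the patient's own request, and cannot be assigned to this clause or to one group.
- **That imputation offers no help.** Earlier scores may enter the imputation model, and sensitivity analyses are promised. Both soften the problem. Which methods are used can properly be left to the analysis plan, but no method recovers events that were never recorded.

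**Conclusion.** The point holds in a limited form. The article allows investigator withdrawal on a ground linked to the patient's condition, stops recording new serious adverse events at that moment, and does not require quality-of-life or mortality follow-up to go on. In an intention-to-treat trial of a one-off operation, that can lose outcome-related data without need.

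The loss of new serious adverse events follows directly from the text. The bias in the primary comparison is conditional: 1 to 3 points of the planned 10 at an assumed 5% v 15% withdrawn and gaps of 10 to 30 points, less where earlier scores are observed or used in imputation, and none if withdrawal and deficits are equal between groups. The documents do not show that withdrawal will be unequal, that the withdrawing investigator is unblinded, or that deaths will be missed. No sample-size figure is affected.

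**What to change.** Keep the welfare clause and amend two paragraphs:

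- **Withdrawals:** state that withdrawal by the investigator ends trial-specific procedures only. Quality-of-life questionnaires (where the patient is willing), vital status, serious adverse events and secondary outcomes continue to be collected to 24 months or death, unless the patient withdraws consent to data collection.
- **Safety evaluation and reporting of adverse events:** let documentation of serious adverse events end at 24 months, at death, or at withdrawal of that consent, in place of premature withdrawal.

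The cost is a short amendment and a few more follow-up contacts. The sample size and the primary analysis stay as they are.

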### Data Safety Monitoring Board (DSMB)

In case of any irregularities for example concerning the frequency or type of serious adverse events reported the principal investigator will inform the members of the independent DSMB without delay. At least once every 12 months, the DSMB will receive a written safety report. The result of the risk/benefit assessment will be reported to the principal investigator including recommendations concerning the continuation of the trial (Members of the DSMB: [name], Centre for Clinical Trials, University of Freiburg, Germany; [name] [name], Director General Surgery, San Giovanni Rotondo, Foggia, Italy; [name], Director Surgical Department Friedrichstadt Hospital, Dresden, Germany).

### Stopping guidelines

No interim analysis is planned for ChroPac. The trial can be prematurely closed by the coordinating investigator in consultation with the steering committee, the Data Safety Monitoring Board and the responsible biometrician for the following reasons:

• The incidence or severity of serious adverse events/morbidity in this trial indicates a potential health hazard caused by the trial treatment.

• It appears that patients' enrolment is unsatisfactory with respect to quality and/or quantity or data recording is severely inaccurate and/or incomplete.

• External evidence demanding a termination of the trial.

In case of premature closure, the ethics committee has to be informed.

#### Monitoring

Clinical Monitoring will be performed by an independent institution already experienced due to the tasks in some other surgical trials (Coordinating Centre for Clinical Trials, Heidelberg, Germany) [17]. Monitoring procedures will be adapted to the trials-specific risk for the patients, interpretation of ICH-GCP (E6) and standard operating procedures to ensure patients' safety and integrity of the clinical data, e.g. primary outcome measure in adherence to study protocol. Prior to the start of the trial all participating centres will be personally trained and introduced into all trial-specific procedures during individual on site initiation visits. Regular on-site monitoring visits are planned at all sites depending on the recruitment rate and quality of the data (approximately one visit per site and year). The investigator must allow the monitor to look at all essential documents and must provide support at all times to the monitor. For 10% of all participants a 100% clinical source data verification for all clinical items is planned. In addition, all procedures will be predefined in a trial-specific monitoring manual. Queries of the data management (e.g. in case of missing values, implausibility etc.) have to be answered by the investigators contemporary to avoid that errors in data capture or entry will be carried forward.

### Ethical considerations

#### Approval

Before the start of the trial, the trial protocol, informed consent document and any other trial documents were submitted to the independent ethics committee on January 30^th ^2009. Ethics approval was reviewed on April 20^th ^2009 and finally issued on May 19^th ^2009.

#### Good Clinical Practice

The procedures set out in this trial protocol, pertaining to the conduct, evaluation and documentation of this trial, are designed to ensure that all persons involved in the trial abide by Good Clinical Practice and the ethical principles described in the current revision of the Declaration of Helsinki. The trial will be carried out in keeping with local legal and regulatory requirements.

#### Registration

The trial protocol was registered http://www.controlled-trials.com and was given a unique number for a world-wide identification of this trial (ISRCTN38973832).

### Translational research

The basic and clinical research aims to identify parameters which influence the clinical outcome and may be useful for prognostic or therapeutical decision making in future with main focus on differences between the two surgical techniques (DPPHR vs. PPW). Serum parameters (20 ml blood) are investigated and pancreatic tissue is analysed by histology, as well as biochemical and molecular biological techniques in a standardised fashion. The molecular alterations are analysed in detail and assessed for its clinical implications. Important parameters of pancreatic tissue in chronic pancreatitis include inflammation and fibrosis and the correlation to pain and pain relief: standardised histological reporting of the degree of inflammation and fibrosis, identification and quantification of expression of pancreatic enzyme activation (e.g. trypsin), cytokines, chemokines, growth factors (e.g. EGFR, TGF), stellate cells and its mediators, collagens are performed.

Since pain is the most frequent indication for pancreatic surgery, a main focus is the investigation of pancreatic and peripancreatic nerves, neurotransmitter, nerve growth factors, and the correlation of pain, chronic inflammation and its relief by pancreatic resection. Potential markers include substance P, NK-1R, CGRP, VIP, NPY, PACAP, bradykinine, eicosanoids. Diabetes mellitus (endocrine insufficiency) has major impact on the long-term outcome of patients with chronic pancreatitis. The correlation of endocrine insufficiency and reduction of endocrine cells and products (insulin, glucagons) in chronic pancreatitis are investigated. Chronic pancreatitis is a known risk factor for pancreatic cancer and premalignant lesions can be detected in inflammatory disease. Serum and tissue markers of carcinogenesis including K-ras, p-53 will be investigated and correlated with histology, clinical outcome, and surgical techniques used. All investigations will be performed centralised and all data stored in a separate database. This will be linked to the clinical database to answer the above-mentioned questions.

## Discussion

Surgical treatment of chronic pancreatitis is indicated in the case of pancreatic head enlargement with local complications (eg, stenosis of the common bile duct and/or main pancreatic duct, duodenal obstruction, compression of retropancreatic vessels), suspicion of malignancy, and most commonly intractable pain [3,4]. Even without inflammatory mass of the pancreatic head, a recent RCT demonstrated surgical treatment of being superior as compared with endoscopic drainage in patients with chronic pancreatitis and a distal pancreatic duct obstruction [10].

The preferred surgical treatment of chronic pancreatitis has been a focus of studies and debate for decades. Several modifications of DPPHR were developed in the last years in order to reduce surgical trauma and compared with PD and PPW in four single centre RCTs for safety and efficacy. The results have been pooled in a systematic review and meta-analysis demonstrating a superiority of DPPHR in terms of QoL, exocrine insufficiency, length of hospital stay, weight gain and occupational rehabilitation [11].

Although DPPHR is technically demanding these techniques seem to be promising due to lesser operative trauma and the gastrointestinal and metabolic integrity by preservation of the duodenum [9]. Therefore, the role of DPPHR versus PD has to be evaluated now in a large-scale pragmatic randomised trial to demonstrate the effectiveness of DPPHR. Consequently, ChroPac was designed to focus on both the surgeons and patients perspectives in the comparison of the two main strategies (DPPHR vs. PD) (Figure 3).

**Figure 3 F3:**

**ChroPac logo**.

### Strength and limitations

The research question of ChroPac is based on sufficient pilot data and since further single centre studies would not be able to strength the external validity, only a multicentre trial can demonstrate the superiority of DPPHR compared with PD in a setting close to daily practice. The Study Centre of the German Surgical Society (SDGC) as the coordinating organisation is experienced and has a proven track record in performing multicentre surgical trials, which highlight the SDGC's central role in trial design and administration and only go to strengthen the feasibility of the proposed trial [18]. An investigators meeting, which was conducted prior to the randomisation of the first patient represents strength of the ChroPac trial: 15 participants of the recruiting departments met at the SDGC in Heidelberg, Germany for a two day educational and practical workshop. While focussing on the explanation of the trials' rationale, surgical procedures, ethics, data management and monitoring within ChroPac, all participants attended surgical procedures for chronic pancreatitis on the second day at the operation theatres at the Department of General, Visceral and Transplantation Surgery, University of Heidelberg, Germany. Overall, the theoretical as well as the hands-on surgical training was highly appreciated and well-rated by the participants (range 1.3 - 2.6 with possible grades from 1 to 6). Moreover, there was general agreement regarding the rationale of the trial, primary outcome measure and feasibility of the trial (range 1.5 - 1.9 with possible grades from 1 to 4). As a result content, comprehensiveness and learning effect was rated to be excellent/very good (range 1.5 - 1.6 with possible grades from 1 to 6). Consequently, ChroPac promises optimal recruitment of study patients with good data quality by a both expertise and conform trial group.

However, the design of ChroPac raised some discussion during the design phase:

Firstly, the choice of the primary efficacy outcome measure *"quality of life" *was debated amongst surgeons, clinical investigators and methodological specialists. As a consequence, QoL will be evaluated by the EORTC QLQ-C30 subscore "physical functioning", which was validated and used in prior RCTs. Besides pain, several other aspects are summarized in this score and assessed from the patients' point of view, which justifies the validity of our primary outcome measure. As a secondary outcome all data of the full EORTC QLQ questionnaire will be collected in order to assess all dimensions of impairments and QoL.

Secondly, the specific trial design was a matter of debate. Since RCTs can be performed as efficacy (or explanatory) as well as effectiveness (or pragmatic) trials, the question to focus on internal validity (generation of the allocation sequence; allocation concealment; blinding; intention to treat analysis; complete outcome reporting and follow-up etc.) or on external validity (generalisability) was of major importance. Thus, performing an efficacy trial promises distinct evaluation of two surgical procedures rather than surgical strategies. ChroPac as an efficacy trial would have required explicitly defined surgical procedures (e.g. Frey versus PPW) and study patients. However, patients' compliance and generalisability is known to be low in these study designs and four single RCTs are already available [19,20]. As a result of the discussions during the investigator meeting the participants agreed and support the pragmatic approach of ChroPac:

Firstly, the available systematic review showed that the comparison of duodenum-preserving techniques versus pancreatoduodenectomy is currently hampered by the methodological weakness of only small available RCTs. Secondly, focussing on a sufficient sample size and optimal data quality the pragmatic approach with compact trial data acquisition and reduced study visits accounts for the compliance of both the investigators and the participating study patients. Thirdly, even a pragmatic approach allows a translational research part for further investigations of nature and mechanisms of chronic pancreatitis. Moreover, ChroPac evaluates a complex intervention and has to consider the expertise of different surgeons, peri-operative treatment regimens and concomitant interventions. Since these varying components reflect the current state-of-the-art treatment of chronic pancreatitis in centres of excellence for pancreatic surgery, ChroPac provides the most efficient evaluation of the present standard.

In summary, the ChroPac-Trial was designed to identify the best surgical strategy for treatment of chronic pancreatitis-either duodenum-preserving head resection or pancreatoduodenectomy. Focussing on a comparison of a general surgical strategy implies that the ChroPac-Trial will not be able to identify the best specific surgical technique in terms of available modifications of either PD or DPPHR. The aim of the ChroPac-Trial was therefore to maximize external validity while sustaining acceptable internal validity, which was accomplished by its pragmatic approach [21].
